#### Cost-effectiveness

To assess *costs*, healthcare utilization will be measured by selected questions from the questionnaires FIMA [67] and FIMPsy [68]. To calculate costs, the measured healthcare utilization will be monetarily valued using standardized unit costs for Germany [69, 70]. Intervention costs will be calculated using a bottom-up approach based on interviews with study personnel on resource use for the development, implementation, and use of the intervention. Resources will be monetarily valued using labor costs for productivity and market prices for goods.

Questionnaires that are not available in Arabic or Farsi will be translated according to the WHO criteria [41].

#### Plans to promote participant retention and complete follow-up {18b}

Participants who end or drop out from treatment will still be invited to participate in the assessments. Participants will be compensated for completing the assessments with up to 60€.

#### Data management {19}

The data safety management plan was approved by the Ethical Committee of the Medical School Berlin (MSB-2023/131). All data is gathered online and will be recorded automatically. Data will be stored on a secure server.

#### Confidentiality {27}

Participants will register on the study platform and will be invited to provide a telephone number (for the diagnostic interview as well as for safety calls, see item 22) and an email address to recover their account. All data is stored on the secure study platform. Data export (excluding personal data) is only available to investigators.

Participants will receive extensive information on what data is assessed, how it is transferred, and where and how long it is stored. Participants provide informed consent.

#### Plans for collection, laboratory evaluation, and storage of biological specimens for genetic or molecular analysis in this trial/future use {33}

N/a: No biological specimens will be collected.

### Statistical methods

#### Statistical methods for primary and secondary outcomes {20a}

Differences in means between the treatment and waitlist conditions on the primary outcome measure (HSCL-25 total score, at post-assessment) and on secondary outcome measures will be tested (superiority) using baseline-adjusted regression models. Unstandardized and standardized between-group differences (*d*) in the primary and secondary outcomes will be reported with appropriate confidence intervals. Moreover, we report dropout rates and provide descriptive statistics on treatment adherence. Moderators and mediators of treatment response will be investigated using regression models.

For the economic evaluation, a cost-utility analysis of CETA-I compared to WL from a healthcare systems perspective will be performed using a modeling approach. A Markov model will be constructed using data on effectiveness (measured by HSCL-25), costs (measured using selected variables from FIMA, FIMPsy), and health-related quality of life (measured by EQ-5D-5L) from the study RCT, complemented by data from the literature. The primary outcome of the economic evaluation will be the incremental cost-effectiveness ratio of CETA-I compared to WL. To analyze uncertainty, univariate and probabilistic sensitivity analyses will be conducted. In addition, budget-impact analyses for CETA-I will be carried out using the same model to estimate the monetary budget impacts of different scenarios. Necessary cost data will be taken from the cost-utility analysis, complemented by data from the literature.

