During treatment, dosage and sequence of modules can also be adapted to the patient’s progress. However, we only allow for specific adaptions. Only modules on safety planning, problem-solving, and substance use can be added when related issues arise. Furthermore, a maximum number of sessions per module is pre-defined (see Appendix 1). Participants will receive a minimum total of 6 sessions and a maximum total of 16 sessions.

Participants can access the online program as an app on their smartphone/tablet and/or as a browser-based version on their desktop computer. Participants are asked to complete one session per week. In each session, participants receive psychoeducation and complete exercises. They receive short written feedback from an online therapist within 48 h after completing a session. Online therapists are trained and supervised Arabic- or Farsi-speaking professionals (bachelor’s or master’s degree in psychology or related subjects). A 2-day training workshop will include training in (a) administering the CETA components; (b) handling the online platform; (c) providing brief, constructive feedback; and (d) enabling crisis management. Supervision will be provided on a biweekly basis.

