#### Strategies to improve adherence to interventions {11c}

## Therapists

Online therapists will receive biweekly supervision. Adherence will further be supported by pre-written feedback messages that online therapists adapt to the individual patient. Adherence will be assessed by analyzing a random selection of written feedback messages. Messages will be analyzed in a qualitative content approach, based on previous work on therapist behavior in guided Internet-based interventions (e.g., [42]). The amount of non-adherent therapist behavior will be assessed.

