#### Sample size {14}

A pragmatic viewpoint was taken in planning the sample size. We assumed that the difference between active treatment and waitlist conditions is between *d* = 0.6–0.8 [30]. Both effects flag clinical meaningful between-group differences. Using an alpha of 5% (two-sided test), randomizing *N* = 44 individuals to each study arm would result in a power of 80% (> 95%) for comparing the WL against the CETA-I condition with *d* = 0.6 (*d* = 0.8). To avoid that the sample becomes too small, we used *n* = 44 for further planning. Two RCTs on CETA [29, 30] reported moderate attrition rates in the treatment (1 to 18%) and waitlist group (4 to 23%). In the RCT on online treatments of Arabic-speaking patients [24], patients showed an attrition rate of 40%. To compensate for dropout, we conservatively assume an attrition rate of 20% in the waitlist group and 40% in the CETA-I condition. Thus, we allocate *N* = 131 individuals (CETA-I: 75; waitlist: 56).

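### The article makes no allowance for therapist clustering, which arises in the CETA-I arm only; if outcomes correlate within therapist, the primary test exceeds its 5% level

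*Protocol article*

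**What the plan says.** **Model.** Section {20a} of the Protocol article states that mean differences on the HSCL-25 total score at post-assessment, and on the secondary outcomes, "will be tested (superiority) using baseline-adjusted regression models". Confidence intervals are promised and described only as appropriate. No therapist term, cluster-robust standard error or partially nested model is named. The section also does not say that observations are treated as independent.

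**Therapist contact.** On CETA-I participants, the text under Tailoring says: "They receive short written feedback from an online therapist within 48 h after completing a session". The Therapists paragraph of {11c} says that adherence is supported by "pre-written feedback messages that online therapists adapt to the individual patient", and that supervision is biweekly. Waitlist participants get the programme only after their 3-month wait ({30}), and their primary endpoint is at week 12 ({12}). At that point therapist contact has occurred in one arm only.

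**Sample size.** Section {14} gives 44 "individuals to each study arm would result in a power of 80% (> 95%) for comparing the WL against the CETA-I condition", at d = 0.6 and d = 0.8 respectively, with a two-sided 5% alpha. The only inflation is for dropout: "we conservatively assume an attrition rate of 20% in the waitlist group and 40% in the CETA-I condition". This leads to 75 in CETA-I and 56 on the waitlist, 131 in all. No design effect or ICC appears.

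**The concern.** With 75 participants allocated to guided treatment, it is close to certain that several share a therapist, although caseloads are not stated. Any stable difference between therapists then makes outcomes within a caseload more alike and raises the variance of the CETA-I mean. The waitlist mean is unaffected.

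A regression without a therapist term estimates its standard error as if this extra variance were absent. Under positive within-therapist correlation the error goes one way: the intervals for the raw difference and for d are too short, and a true null is rejected more often than 5% of the time.

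The article itself gives some reason not to assume a correlation of zero. Working alliance is a candidate mediator ({7} and Mediators of treatment outcome). Therapist non-adherence will be measured ({11c}). Therapists have mixed qualifications and 2 days of training instead of the 10 used in previous CETA trials (Intervention description and Supervision).

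**Working it through.** **1. Reproduce the plan's figures.** Inputs from {14}: alpha 0.05 two-sided, d = 0.6 (SD = 1), power 80%.

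- n per arm = 2(1.960 + 0.842)² / 0.6² = 43.6, rounded up to 44.
- Power with 44 per arm is 80.4% at d = 0.6 and 96.3% at d = 0.8 (t-test: 79.5% and 96.0%).
- The exact t-test n is 44.6, so 45. Dropout inflation gives 45/0.6 = 75 and 45/0.8 = 56.25, against the stated 75 and 56.

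The stated figures therefore reproduce with independent observations and a design effect of 1.

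**2. Variance under one-arm nesting.** Let k be the number of therapists, n₁ and n₂ the analysed numbers in CETA-I and waitlist, m = n₁/k the mean caseload, and ICC the within-therapist correlation given baseline.

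- Variance without a therapist term: 1/n₁ + 1/n₂
- Variance with nesting: [1 + (m − 1)ICC]/n₁ + 1/n₂
- Standard error ratio r = √(second / first)
- Type I error of the nominal 5% test = 2[1 − Φ(1.96/r)]

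**3. Inputs.** n₁ = n₂ = 45, because the planned retention gives 75 × 0.6 = 45 and 56 × 0.8 = 44.8. The documents give neither k nor ICC, so both are assumed: k from 4 to 15, ICC from 0 to 0.10.

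**4. Worked case.** For k = 6 and ICC 0.05:

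- m = 45/6 = 7.5
- design effect in CETA-I = 1 + 6.5 × 0.05 = 1.325
- r = √[(1.325 + 1)/2] = 1.078
- type I error = 2[1 − Φ(1.96/1.078)] = 6.9%

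**5. Range (type I error, %).**

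| Therapists | ICC 0 | 0.01 | 0.02 | 0.05 | 0.10 |
|---|---|---|---|---|---|
| 4 | 5.0 | 5.6 | 6.2 | 8.0 | 11.1 |
| 6 | 5.0 | 5.4 | 5.8 | 6.9 | 8.9 |
| 8 | 5.0 | 5.3 | 5.5 | 6.4 | 7.7 |
| 10 | 5.0 | 5.2 | 5.4 | 6.0 | 7.1 |
| 15 | 5.0 | 5.1 | 5.2 | 5.6 | 6.2 |

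For ICC 0.01 to 0.10, r runs from 1.005 (15 therapists, ICC 0.01) to 1.23 (4 therapists, ICC 0.10).

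**6. Simulation check.** The baseline-adjusted regression was simulated with 20,000 replicates per setting, 45 per arm and an assumed baseline-outcome correlation of 0.5. At ICC 0, 0.01, 0.02, 0.05 and 0.10 the rejection rates were 4.7, 5.7, 6.2, 7.5 and 11.3% with 4 therapists, and 5.0, 5.0, 5.5, 5.9 and 7.1% with 10. These agree closely with the formula, so baseline adjustment does not remove the inflation.

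**The case against.** **Silence is not a statement of independence.** The wording in {20a} is compatible with a random effect, a robust standard error or arm-specific variances, and a statistical analysis plan that is not shown may specify one. This stands. A reader might infer that the plan fixes an ordinary regression with independent, equal-variance errors, but the text does not say so. What remains is that the article names its primary model and sizes the trial, and neither place allows for a nesting that the article's own design creates.

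**The harm is conditional.** A reader might infer that the interval is too narrow as a matter of fact. That requires an ICC above zero, and no figure is given. Adapting messages to the patient is tailoring at patient level and does not by itself create variance between therapists. Brief feedback, pre-written messages, biweekly supervision and module sequences set in a case conference all point to a small ICC. This stands too, and it is why the lower rows and columns of the table are the more plausible ones.

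**Other inferences that the documents do not support.**

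- That the pool of therapists is small: no number is given.
- That therapists make the safety calls: {22} does not say who calls.
- That power falls below 80%: this follows only from an unadjusted comparison, whereas the planned model adjusts for baseline. At d = 0.6, an assumed baseline-outcome correlation of 0.5 and ICC 0.05, power would go from about 90% to 85-87% with 6 to 8 therapists. The result depends on that correlation, which is not given, so no power loss is claimed here.
- That the inflation is larger because all 75 and 56 are analysed: that would need observed outcomes for everyone, but {14} plans for 40% attrition in CETA-I. The formula also ignores the between-imputation variance of the multiple imputation in {20c}.

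**Few therapists may make a mixed model unstable.** This is fair, and it is a reason to accept the model as a sensitivity analysis. The problem is still manageable: a simulated analysis on therapist means with small-sample degrees of freedom held about 5-6% even with 4 to 6 therapists.

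**Conclusion.** The point holds in conditional form. At the primary endpoint the design is partially nested, and the model in {20a} and the sample size in {14} make no allowance for it. If the within-therapist correlation in CETA-I is positive, an analysis without a therapist term understates the standard error. The type I error then lies modestly above 5% for a small ICC and clearly above it only if the ICC is near 0.05 or more and therapists are few. At ICC 0 the test is nominal.

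These sizes rest on assumed therapist numbers and ICCs, equal caseloads and 45 analysed per arm. The direction needs only a positive ICC. The documents do not show that the primary result will be wrong; they leave open a risk that can be closed cheaply before the data are analysed. In an open-label trial with a self-reported primary outcome, it is better to settle the model now than after the results are known.

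**What to change.** In {20a}, state that each CETA-I participant's online therapist will be recorded, and pre-specify a baseline-adjusted partially nested model for the primary outcome with:

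- a therapist random effect in CETA-I only, with each waitlist participant as a singleton;
- a separate residual variance in each arm;
- small-sample degrees of freedom;
- language (Arabic or Farsi) as a covariate, because therapists work in one or the other and the therapist variance could otherwise absorb language differences.

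This model can be primary. At minimum it should be a named sensitivity analysis beside the current regression, with the choice fixed before outcome data are examined. Report the number of therapists and the estimated ICC with the results. In {14}, a sentence acknowledging that no design effect was included would be enough.

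The cost is analysis wording and one identifier per participant. Treatment, assessments and sample size do not change. The interval may be slightly wider, and the therapist variance will be estimated imprecisely if therapists are few.

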#### Interim analyses {21b}

No interim analysis is planned in this trial.

#### Methods for additional analyses (e.g., subgroup analyses) {20b}

To evaluate differential treatment effects, the interaction effects of moderators with treatment on the outcome will be tested. Exploratory mediation analyses will be conducted.

#### Methods in analysis to handle protocol non-adherence and any statistical methods to handle missing data {20c}

For the ITT analyses, missing data will be dealt with using multiple imputations, which is considered a gold standard [71]. Imputation will be done under the missing at-random assumption including different predictors and moderators (as outlined in item 18a) of attrition and outcome, which are assessed at pre-treatment and during treatment. Second, a sensitivity analysis will be performed under more conservative assumptions (e.g., imputed values of non-completers in the intervention condition will be successively increased, and the analysis described above will be repeated) to investigate the robustness of our conclusions concerning between-group differences.

#### Plans to give access to the full protocol, participant-level data, and statistical code {31c}

De-identified participant-level data as well as analysis code will be made publicly available through a research repository (OSF).

### Oversight and monitoring

#### Composition of the coordinating center and trial steering committee {5d}

The research team reviews recruitment rates weekly and meets on a biweekly basis to ensure the integrity of the protocol and conduct of the study. Any significant amendments to the study protocol will be provided to and approved by the Ethics Committee of Medical School Berlin before implementation.

#### Composition of the data monitoring committee, its role, and reporting structure {21a}

An independent Data Safety and Monitoring Board (DSMB) has been established which will meet once a year. This DSMB is independent of all investigators and the funding agency, and no member of the DSMB has direct involvement in the conduct of the study. The DSMB is composed of three researchers familiar with the area of the study. The DSMB will monitor recruitment, the number of dropouts, and all adverse events including study withdrawals.

#### Adverse event reporting and harms {22}

During the trial, symptom deterioration and suicidality will be closely monitored. Participants in the CETA-I condition who score 1 on the suicide item will be invited to complete the safety module that includes follow-up questions. Participants who indicate immediate plans and means, or previous attempts, will be called and guided through the rest of the safety module. Participants who indicate no immediate plans or means and no previous attempts complete the safety module on their own. Participants who score 2 or above on the suicide item will be called directly and guided through the safety module. (2) Participants will be encouraged to communicate potential adverse effects to their online therapists or the PIs. (3) Online therapists will be required to report adverse events immediately to their supervisor and the PIs. 4) The PI will decide if an adverse event must lead to treatment termination. All such cases will be documented and considered for the analyses of the study results.

At post-assessment, we will collect the negative effects caused by the treatment systematically [57]. Participants will complete the NEQ and are encouraged to further note all adverse events that occurred during treatment in an open-ended question. In addition, other markers indicative of adverse events, like hospitalization, as assessed by FIMPsy, and deterioration rates, will be published.

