### Eligibility criteria {10}

We will apply a two-step screening procedure. First, participants will be invited to complete online questionnaires, including the Hopkins Symptom Checklist-25 (HSCL, [35] and the PTSD Checklist for DSM-5 (PCL-5, [36]). Participants scoring above the cutoff on the anxiety and/or depression subscale of the HSCL (> 1.75, [37]) and/or above the cutoff on the PCL-5 (> = [38]) will be invited to take part in a telephone-administered clinical interview. Trained and supervised Arabic- and Farsi-speaking interviewers will administer the Mini-DIPS, a brief, adapted, open-access version of the Anxiety and Related Disorders Interview Schedule (ADIS) based on DSM-5 [39] plus the more elaborate PTSD section of the DIPS [40]. As there are no Arabic or Farsi versions available, we will use our own translations of the Mini-DIPS, realized according to the WHO standards [41].

Inclusion criteria are as follows: (a) age ≥ 18 years; (b) Internet access; (c) primary diagnosis of a depressive disorder (major depressive disorder, persistent depressive disorder), anxiety disorder (generalized anxiety disorder, panic disorder, agoraphobia, social anxiety disorder), or PTSD according to DSM-5; (d) no current psychotic or bipolar disorder; (e) no severe substance use disorder (AUDIT score ≤ 15 for men, ≤ 13 for women; DUDIT score ≤ 25); (f) no serious suicidal ideation at baseline and no suicide attempt within the last 12 months; and (g) no ongoing psychotherapy or unstable psychotropic medication 3 months prior to the study.

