#### Plans for communicating important protocol amendments to relevant parties (e.g., trial participants, ethical committees) {25}

Any amendments to the study protocol would have to be approved first by the Medical School Berlin Ethics Committee. If approved, these changes would have to be reported in the trial registry. Finally, any amendments would be reported in the trial paper.

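### At suicide-item score 1, the trigger for a safety call is narrower than the bar on self-guided work, so an immediate plan without means may trigger no call

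*Protocol article*

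**What the plan says.** The section on adverse event reporting and harms {22} first sets who enters the pathway: "Participants in the CETA-I condition who score 1 on the suicide item will be invited to complete the safety module that includes follow-up questions". It then divides these participants by their answers. One group gets a telephone call: "Participants who indicate immediate plans and means, or previous attempts, will be called and guided through the rest of the safety module". The other does not: "Participants who indicate no immediate plans or means and no previous attempts complete the safety module on their own". A separate rule covers higher scores: "Participants who score 2 or above on the suicide item will be called directly and guided through the safety module".

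Other sections touch on suicidality but do not choose between a call and self-guided work at score 1:

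- Eligibility criteria {10} require "no serious suicidal ideation at baseline and no suicide attempt within the last 12 months".
- Tailoring sets who qualifies for the safety module and allows it to be added during treatment.
- Table 2 lists a weekly single item on suicidal ideation.
- Confidentiality {27} explains that telephone numbers are collected partly for safety calls, and refers back to item 22.

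**The concern.** Two rules that divide a group between two actions should be complements, so that everyone who fails one meets the other. Here they are not. The call rule joins plan and means with *and*. The self-guided rule, in ordinary English, asks for neither. The complement of neither is at least one, not both.

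The case that matters is an immediate plan without means and without a previous attempt. That participant reports more risk than the only profile the text expressly leaves to work alone, but does not meet the stated condition for a call. Means without a plan fall into the same gap. Whether that case needs a call is a lesser matter and one for clinical judgement.

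The split is made on answers given inside the module, since the call covers only the rest of it. Whoever programs or follows the branching needs an instruction for every pattern of answers.

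**Working it through.** The protocol gives no figure to reproduce. The check is a truth table.

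**Inputs**, all from section {22}, for score 1 in the CETA-I arm: P = immediate plan, M = means, A = previous attempt.

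- Called = (P and M) or A
- Alone = not P and not M and not A

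**Three separate yes/no questions (2 × 2 × 2 = 8 patterns)**

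| P | M | A | Called | Alone | Mode |
|---|---|---|---|---|---|
| no | no | no | no | yes | alone |
| yes | no | no | no | no | none |
| no | yes | no | no | no | none |
| yes | yes | no | yes | no | called |
| any | any | yes (4 patterns) | yes | no | called |

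Called 1 + 4 = 5, alone 1, unassigned 2; 5 + 1 + 2 = 8.

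**Means asked only after a plan.** There are three plan/means states (no plan; plan without means; plan with means), so 3 × 2 = 6 patterns. Called 3 + 1 = 4, alone 1, unassigned 1. The unassigned pattern is plan without means and without attempt.

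**Plan and means as one compound question.** There are 2 × 2 = 4 patterns. Called 3, alone 1, unassigned 0.

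**Possible repairs**

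| Repair | Separate questions (8) | Means after plan (6) |
|---|---|---|
| Call if P or M or A; self-guided sentence unchanged | 7 called, 1 alone, 0 unassigned | 5 called, 1 alone, 0 unassigned |
| Call if P or A; self-guided sentence unchanged | 6 called, 1 alone, 1 unassigned (means only) | 5 called, 1 alone, 0 unassigned |
| Call if P or A; alone if not P and not A (both sentences changed) | 6 called, 2 alone, 0 unassigned | 5 called, 1 alone, 0 unassigned |

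**Does another rule fill the gap?** The direct call at score 2 or above excludes score 1 by definition. The baseline exclusion does not reach a plan that arises later. Tailoring settles who receives the module, not how. The weekly item feeds the pathway but does not divide it. The therapist's response is written and depends on a completed session: "They receive short written feedback from an online therapist within 48 h after completing a session". None of these assigns the mode.

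**The case against.** The strongest objection is that the gap depends on material not shown. The wording and branching of the follow-up questions are not in the article, and with a compound question no pattern is unassigned. Such detail may well sit in the full protocol or the platform specification. This stands as a limit on certainty. It does not remove the point, because the article states both branches with their triggers, and as stated they do not fit together.

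A second objection is that the text is a loosely worded two-way split whose intent is clear. Much of this stands. A reader might infer that the protocol leaves a participant with an immediate plan to work alone, or that call and self-guided work are equally open readings. The document does not support either inference. The self-guided sentence in its plain sense admits only people with neither plan nor means, so it already bars this participant from working alone. Closing the gap the other way would mean reading that sentence as *not both*, which is not ordinary English. What remains is that the call sentence, applied literally, does not trigger the call that the bar implies.

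A third objection concerns the surrounding safeguards: exclusion of serious ideation and recent attempts at baseline, weekly monitoring, therapist training in crisis management, biweekly supervision, immediate reporting of adverse events, and the direct call at score 2 or above. Every score-1 participant in the CETA-I arm is also invited to the module, so it would be wrong to infer that anyone is left without a safety response; only its mode is open. These safeguards make an overlooked case less likely and keep the point minor, but they do not supply the missing instruction.

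Finally, requiring a call for means alone would settle a clinical threshold that the defect does not settle. That is fair, and the fix leaves the choice to the clinical team.

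**Conclusion.** The point holds in a limited form. At score 1 without a previous attempt, the call trigger is narrower than the complement of the self-guided condition. If plan and means are asked separately or in sequence, a participant with an immediate plan but no means may not work alone under the plain wording, yet meets no condition for a call.

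The size is 2 of 8 answer patterns with separate questions, 1 of 6 with sequential questions and 0 of 4 with a compound question. These counts describe the rule, not how often the case will occur; the share of participants affected is not given. The conclusion rests on the ordinary reading of the self-guided sentence and on a question format other than the compound one.

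This is a minor but real correction to a safety rule. Sample size, power and the primary analysis are untouched.

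**What to change.** In section {22}, align the call sentence with the self-guided sentence, so that any immediate plan or any previous attempt triggers a call. The simplest edit replaces *and* with *or* between plans and means in the call sentence and leaves the self-guided sentence alone.

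That edit also calls participants who report means only. If the clinical team does not want this, it should state the mode for means alone in both sentences. Narrowing the call sentence to plans or attempts without touching the self-guided sentence would leave means-only participants unassigned when the questions are separate.

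Then confirm that the platform's branching follows the corrected rule. If it already calls on any immediate plan and the means-only mode is settled, only the wording changes.

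The cost is a short amendment and a check of the platform. Section {25} sets the procedure: "Any amendments to the study protocol would have to be approved first by the Medical School Berlin Ethics Committee", followed by reporting in the registry and the trial paper. There may be extra safety calls, in a number that cannot be estimated from the document. Telephone numbers for such calls are already requested.

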#### Criteria for discontinuing or modifying allocated interventions {11b}

A participant may withdraw from the study at any time, for any reason, specified or unspecified, and without penalty or loss of benefits. Furthermore, the principal investigator has the right to discontinue the treatment of participants in case of the following: (a) adverse events (e.g., suicide attempt, severe major depression) that impede treatment or impair the interpretability of the study results or (b) reasons precluding attendance of scheduled treatment modules. Date of discontinuation, all recorded results at that time, and, if known, the reasons for discontinuation will be documented. All participants will be followed up at each assessment point after discontinuation according to the intention-to-treat principle.

We will not allow for the modification of allocated interventions.

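### The only instruments that ask participants systematically about negative effects of treatment are given once, at post-assessment, which the plan assumes 40% of the CETA-I arm will not provide

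*Protocol article*

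**What the plan says.** Under Adverse event reporting and harms {22} the protocol article states: "At post-assessment, we will collect the negative effects caused by the treatment systematically". The instruments named are the NEQ and an open question on adverse events during treatment. In Table 2 (Outcomes {12}) the NEQ is marked once, at Post. The same harms section adds that other markers, "like hospitalization, as assessed by FIMPsy, and deterioration rates, will be published"; it gives no time point for the deterioration rate.

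Sample size {14} says: "we conservatively assume an attrition rate of 20% in the waitlist group and 40% in the CETA-I condition". The resulting allocation is "CETA-I: 75; waitlist: 56".

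Several provisions bear on people who leave. Section {11b} provides for assessment to continue after discontinuation and says that, "if known, the reasons for discontinuation will be documented". Section {18b} keeps inviting people who stop treatment to the assessments and pays up to 60€ for completing them. Section {22} also provides for monitoring of deterioration and suicidality during the trial and for immediate reporting of adverse events by therapists. Section {21a} has the monitoring board review adverse events, including withdrawals.

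**The concern.** Negative effects of a psychological treatment are a plausible reason for leaving it. If the form that asks about them is shown only at the end, those who left for that reason are the people least certain to be asked successfully. The published negative-effect profile of CETA-I would then rest on a selected part of the arm.

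This is a matter of the schedule, so it cannot be left to an analysis plan: answers that were never requested before a participant was lost cannot be recovered by analysis. The stake is the credibility of the harms statement for a treatment meant to be scaled up in a vulnerable population. The primary efficacy result is not affected.

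**Working it through.** **1. What the 40% stands for.** Inputs from Sample size {14}: two-sided alpha 5%, d = 0.6 to 0.8, 44 per arm, attrition 40% (CETA-I) and 20% (waitlist).

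- Normal approximation: n = 44 per arm at d = 0.6, with power 80.4% at d = 0.6 and 96.3% at d = 0.8. With the t test, power is 79.5% and 96.0%, and the required n is 44.6, i.e. 45.
- Inflation by n / (1 − attrition): 45 / 0.6 = 75 and 45 / 0.8 = 56.25. The stated 75 + 56 = 131 is reproduced to rounding. Starting from 44 gives 74 + 55 = 129.

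The attrition figure is used to preserve the number analysable for the post-assessment endpoint. It therefore works as loss of the post-assessment, which is also where the NEQ and the open question sit.

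**2. Expected numbers without the post-assessment.**

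- CETA-I: 75 × 0.4 = 30 missing, 45 assessed.
- Waitlist: 56 × 0.2 = 11.2 missing, about 45 assessed.

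**3. What can be said about the CETA-I rate without assumptions about those missing.** Let p be the rate among responders, who are 60% of the arm. The rate in all 75 lies between 0.6p (no non-responder affected) and 0.6p + 0.4 (all affected). For an illustrative p = 10%, that is 6% to 46%.

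**4. How far the reported rate could be off.** Let r be the ratio of the rate in non-responders to that in responders. The documents do not give r, so it is an assumption. Reported rate / true rate = p / (0.6p + 0.4rp) = 1 / (0.6 + 0.4r).

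| r (assumed) | reported / true | true rate if 10% is reported |
|---|---|---|
| 0.5 | 1 / 0.8 = 1.25 | 8% |
| 1 | 1.00 | 10% |
| 2 | 1 / 1.4 = 0.71 | 14% |
| 3 | 1 / 1.8 = 0.56 | 18% |

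Under-reporting needs r above 1. That is plausible, but the plan contains nothing that establishes it.

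**5. Rare effects.** If no case of an effect is seen, the one-sided 95% upper limit is 1 − 0.05^(1/n): 6.4% with n = 45, against 3.9% with n = 75. This loss of precision occurs even when r = 1.

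**6. Other harms sources, set side by side (Table 2 and section {22}).**

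| Source | When | Asks about negative effects of treatment? |
|---|---|---|
| NEQ, open question | Post only | Yes |
| FIMPsy (hospitalisation) | Baseline, post, 6 months (CETA-I only) | No |
| HSCL-25 (possible basis for deterioration) | Baseline, week 5, post; 3 and 6 months (CETA-I only) | No |
| PHQ-4, short PCL-5, risk items | Weekly | No |
| Reports through therapists or PIs | During the trial | Only if the participant raises it |

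Only the first row asks every participant the question, and only that row has a single time point.

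**The case against.** The strongest reply is that the protocol does not rely on one visit for safety. Deterioration and suicidality are monitored throughout, therapists must report adverse events at once, and the monitoring board sees adverse events and withdrawals. People who stop treatment are still invited and paid to complete assessments, so post-assessment responders will include some who stopped. The 40% is called conservative, and the CETA trials cited in the same section had 1 to 18% attrition in the treatment arm. An exit form would also go partly to people who already ignore invitations.

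Most of this stands, and it limits the point. It does not remove it. Spontaneous reporting is weakest for someone who has gone silent, and reasons for stopping are recorded only where known. The sponsor planned for 40% loss with these retention measures in the same protocol.

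A reader might infer more than the text supports:

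- **That all harms measures hang on the post-assessment.** They do not. The deterioration rate has no stated time point, HSCL-25 is also taken at week 5, and FIMPsy is repeated at 6 months in CETA-I.
- **That harms would be counted mainly in people who tolerated the treatment.** The 40% is loss of assessment, not stopping for intolerance.
- **That CETA-I would wrongly look safer than the waitlist.** If the true waitlist rate were 12% and the same ratio held there, the observed rate would be 12 / (0.8 + 0.2 × 2) = 10.0% at r = 2 and 12 / (0.8 + 0.2 × 3) = 8.6% at r = 3. Neither exceeds an observed 10% in CETA-I. A waitlist comparison also means little for a form about effects of treatment.

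Whether imputation extends to deterioration rates, and how denominators are shown, are matters for an analysis plan that is not at hand. They are not part of this point.

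**Conclusion.** The point holds for the NEQ and the open adverse-event question. They are scheduled once, and on the plan's own figures about 30 of 75 CETA-I participants would not answer them. Negative-effect rates may be too low, but neither the direction nor the size of a bias follows from the documents. A reported rate at 71% or 56% of the true one requires the assumption that non-responders are affected two or three times as often. What follows without that assumption is the wide range of compatible rates (6% to 46% around an observed 10%) and the weaker limit for effects not seen (6.4% instead of 3.9%). Both rest on attrition reaching the planned 40%; with better retention they shrink. This is a worthwhile, inexpensive improvement to the schedule and does not undermine the trial.

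**What to change.** In CETA-I, present the NEQ and the open adverse-event question at two further points: at the existing week-5 assessment, and automatically when a participant stops treatment or becomes inactive. Add these to Table 2 and to section {22}. Keep the post-assessment administration: with 6 to 16 sessions at one per week, week 5 falls before the end of even the shortest course and can show only early effects.

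The gain depends on how many of the 30 answer at least once, which the documents do not allow one to predict. If none do, 45 of 75 have data; if half do (an assumption), 45 + 15 = 60 of 75; if all do, 75.

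The cost is small, since the form has 20 items and is already planned for the trial platform. The downsides are a slightly longer week-5 assessment in CETA-I and an uncertain response to the exit form.
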